#### 2.4.1. Primary Outcomes

Patients' states of consciousness (in Glasgow consciousness disorder table of GCS score) are observed at the following time points (before treatment, immediately after treatment, and 30 minutes, 1 hour, and 4 hours after treatment) in two groups. And patients' carboxyhemoglobin (COHb) concentration of venous blood samples is detected at the following time points (before treatment and 1 hour and 4 hours after treatment) in two groups.

#### 2.4.2. Secondary Outcomes

Patients' basic vital signs including temperature (*T*), pulse (*P*), respiration (*R*), and blood pressure (BP) are observed at the following time points (before treatment, immediately after treatment, and 30 minutes, 1 hour, and 4 hours after treatment) in two groups.

### 2.5. Sample Size and Statistical Analysis

Sample size will be based on the primary outcome. According to our pilot trial and review of the literature [8], the average defecation rate of patient with COHb was 22.40% with a standard deviation of 3.65% and the average defecation rate of patient with COHb was 17.78% with a standard deviation of 5.68%. To detect COHb% difference, we need a sample size of 30 in each group (*α* = 0.05, *β* = 0.10) [13]. To allow 5% for loss to follow-up, our proposed trial requires 62 patients (31 for each group).

Statistical analysis of all data will be done by Department of Public Health Statistics, which is blinded to this trial, using SPSS 19.0 software packages to analyze the data. All data are provided as mean ± standard deviation. The level of significance was set a *P* value less than 0.05. All of the analyses will be based on both an intention-to-treat analysis and a treated-per-protocol analysis. The intention-to-treat population was defined as the patients who are randomized and received at least one treatment session. The per-protocol population was defined as the patients who have no major protocol violations in the set. Both results of analysis will be compared to check whether the results are consistent.

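### The 30 per group does not follow from the stated COHb means, SDs, alpha and beta, the inputs are mislabelled with no arm or time, and the 5% loss allowance is rounded down

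*Protocol article*

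**What the plan says.** The sample size paragraph in section 2.5 gives two inputs, attributed to a pilot trial and the literature: "the average defecation rate of patient with COHb was 22.40% with a standard deviation of 3.65" percent, and "the average defecation rate of patient with COHb was 17.78% with a standard deviation of 5.68" percent. It then states "To detect COHb% difference, we need a sample size of 30 in each group", with alpha 0.05 and beta 0.10, and adds "To allow 5% for loss to follow-up, our proposed trial requires 62 patients (31 for each group"). The analysis paragraph of the same section sets the significance level: "The level of significance was set a *P* value less than 0.05".

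The section does not state the test, the sidedness or which SD entered the formula. Section 2.4.1 names two primary outcomes, GCS and COHb, and has COHb measured before treatment and at 1 and 4 hours after it.

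**The concern.** A sample size statement should let a reader get from inputs to result. This one fails in three ways.

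- The two means, two SDs, alpha and beta do not give 30 by any of the usual routes tried below.
- Both inputs carry the same label, a defecation rate. That quantity is not among the outcomes in sections 2.4.1 and 2.4.2 or Table 1. Neither value has an arm or a time. The pair could be control against bloodletting at 1 hour, the same at 4 hours, or before against after in one group. In the last case the calculation would not describe a between-group comparison at all.
- The step from 30 to 31 does not deliver the 5% allowance it claims.

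At stake is whether the trial's only justification of its size, and the error rate attached to it, can be relied on.

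**Working it through.** **Inputs (all from section 2.5).** Means 22.40 and 17.78; SDs 3.65 and 5.68; alpha 0.05; beta 0.10, so power 0.90; equal groups; 5% loss. Assumed, because not stated: the two values are the two arms at one time after treatment, and the test is two-sided.

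**Step 1. Effect size.**
- Difference = 22.40 − 17.78 = 4.62
- SD combining both values = √((3.65² + 5.68²)/2) = √((13.3225 + 32.2624)/2) = √22.792 = 4.774
- Standardised difference = 4.62/4.774 = 0.968

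**Step 2. Attempt to reproduce 30.** Normal formula: n per group = 2 × (z₁₋α/₂ + z₁₋β)² × (SD/difference)².
- Both SDs: 2 × (1.960 + 1.2816)² × (4.774/4.62)² = 22.44, so 23. By the noncentral t distribution, 23 gives 89.4% and 24 gives 90.7%, so 24.
- SD 5.68 in both arms: 2 × (1.960 + 1.2816)² × (5.68/4.62)² = 31.8, so 32 (t-test: 33).

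All variants tried, for 90% power:

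| Variant | Normal | t-test |
|---|---|---|
| Two-sided 0.05, both SDs | 23 | 24 |
| Two-sided 0.05, average of the SDs (4.665) | 22 | 23 |
| Two-sided 0.05, smaller SD (3.65) | 14 | 15 |
| Two-sided 0.05, larger SD (5.68) | 32 | 33 |
| One-sided 0.05, both SDs | 19 | 20 |
| One-sided 0.05, larger SD | 26 | 27 |
| Two-sided 0.025, both SDs (contradicts the stated alpha) | 27 | 28 |

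None returns 30. A common SD of 5.52 would be needed to give exactly 30 by the normal formula, and no such figure appears.

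**Step 3. Power at 30 per group, two-sided 0.05.**
- Both SDs: 96.3% (normal), 95.8% (t-test), 95.7% (Welch). Beta is about 0.04.
- SD 5.68 in both arms: 88.3% (normal), 87.2% (t-test). Beta is about 0.12 to 0.13.

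**Step 4. Loss to follow-up.**
- 30/(1 − 0.05) = 31.58, so 32 per group and 64 in total. The cruder 30 × 1.05 = 31.5 also rounds up to 32.
- 31 × 0.95 = 29.45 per group, and 62 × 0.95 = 58.9 in total, against the 60 said to be needed.
- Loss that 31 per group can absorb while keeping 30: 1 − 30/31 = 3.2%.
- t-test power at 29 evaluable per group: 95.2% with both SDs, 86.1% with SD 5.68 in both arms.

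**The case against.** The strongest reply is that the figure of 23 to 24 rests on conventions the article does not state, and that its method reference is not available here. Taking the larger SD for both arms is a defensible cautious choice, and it lands within two or three patients per group of 30. Rounding up from 24 cannot be excluded either; 24/0.80 is exactly 30, though the article states a 5% allowance and applies it after reaching 30. So what can be shown is that 30 is not reproducible as written. How it was obtained cannot be shown. That part of the reply stands.

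It is also fair that the intended variable can be guessed: both input phrases mention COHb, and the sentence that follows speaks of a COHb difference and a size for each group. This favours the two-arm reading but does not supply the arm or the time. The loss shortfall is one patient per group and barely moves the power.

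A reader might infer from the mismatch that the trial is too small. The document does not support that: on the plain reading, 30 per group exceeds the 90% target. Nor does the wrong label show the power to be wrong; it makes it uncheckable.

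**Conclusion.** Wrong as written. Under a two-sided comparison of two arms, the stated inputs require 23 to 24 per group if both SDs are used and 32 to 33 if the larger SD is used throughout. Power at 30 is then about 96% or 87 to 88%, so beta is about 0.04 or 0.12 to 0.13, and on neither reading the stated 0.10. The mismatch is conservative on the plain reading and slightly unfavourable on the other.

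These figures hold only if the two values are the two arms at the same time after treatment, which the article does not say. That gap is the weightiest part of the point, because without it no power figure can be confirmed. The loss error holds whatever SD, test or sidedness was used, but it is small: 31 per group covers 3.2%, not 5%.

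The calculation concerns COHb only. The article gives no mean or SD for GCS, so nothing here speaks to power for that outcome or to how two primary outcomes share the significance level.

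**What to change.** Rewrite the sample size statement in section 2.5:

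1. Replace the defecation label with COHb (%), and give the arm and the time after treatment for each mean and SD.
2. State the test, its sidedness and the SD used.
3. Once the values are confirmed as the two arms at one time, restate the power at 30 evaluable per group: about 96% with both SDs, or about 87% (t-test) if SD 5.68 is assumed in both arms. If they prove to be something else, such as before and after in one group, the calculation has to be redone from suitable inputs.
4. State that 31 per group covers about 3% loss, and that 5% loss leaves about 29 evaluable per group, with about 95% power using both SDs.

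The cost is a rewrite of about two sentences after a check of the pilot and literature figures. With the inputs confirmed, enrolment stays at 62.

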### 2.3. Intervention

#### 2.3.1. Standard of Care Group

The standard of care group will receive general first aid treatment including hyperbaric oxygen therapy (HBO) about 45–60 minutes, citicoline 1 g intravenously once daily, and naloxone 0.4 mg intravenously every 12 hours.

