#### 2.3.2. Bloodletting Group

The bloodletting group will receive general first aid treatment, the same as control group. Meanwhile, the bloodletting group will be treated with THJP on admission immediately before hyperbaric oxygen therapy. The order of puncture and bloodletting should be set. In this study, we decide to puncture and bloodlet the left hand first and then the right hand in the order of Shaoshang (LU11), Shangyang (LI1), Zhongchong (PC9), Guan Chong (TE1), Shaochong (HT9), and Shaoze (S11). And the amount of bloodletting at each point is one drop. At the same time, we choose a unified model needle. The location of acupoints is as follows [12].

*Shaoshang (LU11)*. It is on the thumb, radial to the distal phalanx, 0.1 F-cun proximal-lateral to the radial corner of the thumb nail, at the intersection of the vertical line of the radial border and the horizontal line of the base of the thumb nail. 

*Shangyang (LI1)*. It is on the index finger, radial to the distal phalanx, 0.1 F-cun proximal-lateral to the radial corner of the index fingernail, at the intersection of the vertical line of the radial border of the fingernail and the horizontal line of the base of the index fingernail. 

*Zhongchong (PC9)*. It is on the middle finger, at the centre of the tip of the middle finger, 0.1 F-cun proximal-lateral to the radial corner of the thumbnail, at the intersection of the vertical line of the radial side of the nail and the horizontal line of the base of the finger nail. 

*Guan Chong (TE1)*. It is on the ring finger, ulnar to the distal phalanx, 0.1 F-cun proximal to the ulnar corner of the fingernail, at the intersection of the vertical line of the finger side of the nail and the horizontal line of the base of the finger nail. 

*Shaochong (HT9)*. It is on the little finger, radial to the distal phalanx, 0.1 F-cun proximal-lateral to the radial corner of the little finger nail, at the intersection of the vertical line of the radial border of the nail and the horizontal line of the base of the little finger nail. 

*Shaoze (S11)*. It is on the little finger, ulnar to the distal phalanx, 0.1 F-cun proximal-medial to the ulnar corner of the little finger nail, at the intersection of the vertical line of ulnar border of the nail and the horizontal line of the base of the little finger nail.

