## 3. Discussion

According to TCM theory, the body is regarded as a whole. It is composed of internal and external organs. These organs connect with each other by special ways called meridians [14]. Twelve Hand Jing Points are located at the end of fingers like the source of spring. Jing points are compared to the underground spring and the pulses here are so small.

*Well* or* Jing* is like underground water. It is described that the pulse is so small. The body of each of the twelve meridians has a well hole; they are also called* Jing Points*. Puncturing and bloodletting at Twelve Hand Jing Points are traditional Chinese medicine first aid measures used in various types of aid for more than 3000 thousand years in history. Some studies have indicated that acupuncture can play a therapeutic role in awaking consciousness disorders. From the clinical trials, we can see the potential for cerebral protection [8, 15–18]. However, this deduction is insufficient and may lead to bias because of the poor quality which is without a standardized acupuncture protocol. Therefore, we designed a multicenter randomized controlled protocol and expected to provide convincing evidence to clarify the efficacy of THJP for first aid treatment of acute carbon monoxide. Acupuncture is a nontoxic, economical intervention with minimal adverse effects [19], which has been shown to remain effective even for a few months after the therapy [20]. One of the limitations in this trial design is the nonblinding of the patients and acupuncturists. Due to the characteristics of THJP, it is impossible to blind the patients and acupuncturists. However, we develop a rigorous methodology in other aspects of the study.

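### The set labelled intention-to-treat is a modified set that requires an undefined treatment session after randomisation, and no analysis of all randomised patients is planned

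*Protocol article*

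**What the plan says.** Section 2.5 of the protocol article names two analysis sets and uses both throughout: "All of the analyses will be based on both an intention-to-treat analysis and a treated-per-protocol analysis". The first is defined thus: "The intention-to-treat population was defined as the patients who are randomized and received at least one treatment session". The second is defined thus: "The per-protocol population was defined as the patients who have no major protocol violations in the set". The safeguard is a comparison of the two: "Both results of analysis will be compared to check whether the results are consistent". Section 2.5 does not say what a treatment session is.

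Treatment is described in section 2.3. For controls (2.3.1): "The standard of care group will receive general first aid treatment including hyperbaric oxygen therapy (HBO) about 45–60 minutes". For the experimental arm (2.3.2): "The bloodletting group will receive general first aid treatment, the same as control group". In addition, "the bloodletting group will be treated with THJP on admission immediately before hyperbaric oxygen therapy". Only this one application of THJP is described; that it is the only one is a fair inference, though the article does not say so outright.

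On blinding, section 3 concedes: "One of the limitations in this trial design is the nonblinding of the patients and acupuncturists".

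**The concern.** Randomisation makes the arms comparable as randomised. Once membership of the analysis set depends on what was delivered afterwards, that guarantee holds only if non-delivery is unrelated to arm or unrelated to prognosis. Open treatment gives no assurance of either.

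In a trial with many sessions, a one-session minimum removes few patients. Here the experimental component appears to be a single event, so missing it means missing the whole experimental treatment. Whether such a patient stays in the set called intention-to-treat turns on a term that the plan leaves open, and that could be settled after data have been seen.

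At stake is whether the headline comparison of COHb and Glasgow Coma Scale score is a comparison of the randomised groups.

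**Working it through.** **1. Three readings of a session, set against sections 2.3.1 and 2.3.2**

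| Reading | Bloodletting patient who misses THJP but gets first aid | Control patient who gets first aid | Consequence |
|---|---|---|---|
| THJP only | dropped | dropped | No control qualifies, so this cannot be meant |
| Any study treatment | kept | kept | Symmetric; almost nobody is lost |
| The treatment assigned to the arm | dropped | kept | Exclusion falls almost wholly on one arm |

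Only the third reading creates a difference between arms. Under all three, a randomised patient who receives nothing is left out.

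**2. The plan's own figures, used only for scale**

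Inputs from section 2.5: means 22.40% and 17.78%, SDs 3.65% and 5.68%, α = 0.05, β = 0.10, 30 per group, 31 after the allowance for loss.

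- Difference: 22.40 − 17.78 = 4.62 points.
- Pooled SD: √((3.65² + 5.68²)/2) = 4.77.
- n per arm = 2(1.96 + 1.2816)² SD² / 4.62². With SD 5.68 this is 31.8, so 32. With SD 4.77 it is 22.4, so 23.

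The stated 30 is within 2 patients of the result for the larger SD. It does not depend on how intention-to-treat is defined.

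**3. Possible bias under the third reading**

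Suppose k of 31 bloodletting patients are dropped and nobody is dropped from control. If the dropped patients' COHb would have differed from that of the retained patients by a gap g, then

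bias in the mean difference = (k/31) × g.

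If k = 0 or g = 0, the bias is zero. The document gives neither value, so both are assumptions:

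| k | g = 5 points | g = 10 points |
|---|---|---|
| 1 | 0.16 | 0.32 |
| 2 | 0.32 | 0.65 |
| 3 | 0.48 | 0.97 |
| 5 | 0.81 | 1.61 |

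**4. An illustration with partial selection**

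There is no treatment effect, 31 patients per arm and SD 4.77. The k patients with the highest value of a severity score are dropped from one arm, and the score has correlation ρ with later COHb. The expected shift is

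ρ × SD × (sum of the k largest expected normal order statistics of 31) / (31 − k).

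The sums are 3.69 for k = 2 and 5.07 for k = 3. With ρ = 0.5:

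- k = 2: 0.5 × 4.77 × 3.69 / 29 = 0.30 points, which is 0.30/4.62 = 7% of the planned difference.
- k = 3: 0.5 × 4.77 × 5.07 / 28 = 0.43 points, which is 9% of it.

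Simulated null trials with a two-sided t-test at 0.05 give a type I error of about 6% for k = 2 and 6.6% for k = 3. With ρ = 1, where the patients with the worst outcomes are exactly those removed, the figures are 0.60 points and 8.9%, and 0.87 points and 12.5%. That is an upper bound for these k, not an expectation.

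**5. Power if every randomised patient is kept**

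Assume that k untreated bloodletting patients gain no effect. The effect becomes 4.62 × (31 − k)/31, and power = Φ(effect / (SD × √(2/31)) − 1.96).

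| k | Diluted effect | Power, SD 4.77 | Power, SD 5.68 |
|---|---|---|---|
| 0 | 4.62 | 96.8% | 89.3% |
| 2 | 4.32 | 94.6% | 85.0% |
| 3 | 4.17 | 93.1% | 82.4% |

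**The case against.** The strongest reply is that the text states one rule for both arms, and that the bloodletting arm receives the same first aid as control. On the natural reading that any study treatment is a session, a patient who misses THJP stays in, almost nobody admitted is lost, and the set differs from strict intention-to-treat in name more than in content. Treatment also starts on admission, which leaves little time for patients to go untreated. This stands as far as it goes: the asymmetry between arms depends on one reading of an undefined term. It does not remove the fact that a conditional set carries the intention-to-treat label.

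A reader might infer four stronger things that the document does not support:

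- *That the analysis is as-treated.* Nobody is reassigned to the treatment received; patients are excluded. Modified intention-to-treat is the right term.
- *That the consistency check cannot work.* If the assigned treatment is what counts, both sets omit patients who missed THJP, and agreement would say nothing about this bias. If any treatment counts, such a patient stays in one set and could leave the other, and the check is informative.
- *That the sickest patients miss THJP, so the bias favours it.* This is plausible, but the article gives no rate of or reason for omission. A refusal, for instance, need not track severity.
- *That type I error reaches 9% to 12%.* That requires exclusion to predict perfectly a COHb value measured 1 to 4 hours after treatment.

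It could also be said that the choice of a primary set belongs in the statistical analysis plan. That is fair, and its absence is not the complaint. The complaint is that neither of the two sets stated contains all randomised patients.

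**Conclusion.** The point holds as a wrong definition, not as proof of bias. The set that section 2.5 calls intention-to-treat conditions on a post-randomisation event, and every planned analysis uses either that set or per-protocol.

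The consequence ranges from nil to modest. It is nil if nobody is dropped, if dropping is unrelated to prognosis, or (very nearly) if any study treatment counts as a session. If the assigned treatment is meant, and 2 to 3 of 31 patients are lost from one arm with selection moderately related to outcome, the shift is about 0.3 to 0.4 COHb points and the type I error about 6% to 7%. The number dropped, the correlation of 0.5 and the restriction to one arm are all assumptions. The document fixes neither the size nor the direction.

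**What to change.** In section 2.5, define the intention-to-treat population as all randomised patients, analysed in the arm assigned, whether or not THJP or first aid was given, and use it for the main comparison of both primary outcomes. Keep the set requiring at least one session under the name modified intention-to-treat, state what counts as a session in each arm, and report it with per-protocol as a sensitivity analysis.

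The cost is a change of wording, plus outcome measurement at the scheduled times in any patient who goes untreated. Planned N stays 62. The effect is slightly diluted if some bloodletting patients do not receive THJP: with 2 of 31 untreated, from 4.62 to 4.32 points, and power from 96.8% to 94.6% at the pooled SD, or from 89.3% to 85.0% at the larger SD.

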## Figures and Tables

**Figure 1 fig1:**
[figure not shown]
Trail flow chart.

**Table 1 tab1:** Trial processes chart.

Times	Baseline		Treatment		
	−1	0	0.5 h	1 h	4 h
Patients					
Medical history	*√*				
Physical examination	*√*	*√*	*√*	*√*	*√*
Laboratory examination	*√*			*√*	*√*
Informed consent	*√*				
Randomization	*√*				
Intervention					
Standard of care group	General first aid treatment				
Bloodletting group	General first aid treatment + THJP				
*Outcome *					
primary outcomes					
GCS	*√*	*√*	*√*	*√*	*√*
COHb	*√*			*√*	*√*
Secondary outcomes					
T	*√*	*√*	*√*	*√*	*√*
P	*√*	*√*	*√*	*√*	*√*
R	*√*	*√*	*√*	*√*	*√*
BP	*√*	*√*	*√*	*√*	*√*
Trial evaluation					
Safety of hand pricking blood therapy	*√*	*√*	*√*	*√*	*√*
Adverse event	*√*	*√*	*√*	*√*	*√*
Reasons of drop-outs or withdrawals					*√*
Patient's compliance					*√*

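### The population labelled intention-to-treat requires receipt of an undefined treatment session, so bloodletting patients who miss THJP could be excluded with no matching exclusion among controls

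*Protocol article*

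**What the plan says.** Section 2.5 of the protocol article names two populations. The first: "The intention-to-treat population was defined as the patients who are randomized and received at least one treatment session". The second: "The per-protocol population was defined as the patients who have no major protocol violations in the set". Both are used throughout: "All of the analyses will be based on both an intention-to-treat analysis and a treated-per-protocol analysis". The two sets of results are then compared for consistency. No set of all randomised patients is defined anywhere.

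The treatments are set out in section 2.3 and Table 1.

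- Control arm (2.3.1): "The standard of care group will receive general first aid treatment including hyperbaric oxygen therapy (HBO) about 45–60 minutes", together with two drugs. No sham or matching procedure is described.
- Bloodletting arm (2.3.2): "The bloodletting group will receive general first aid treatment, the same as control group". In addition, "the bloodletting group will be treated with THJP on admission immediately before hyperbaric oxygen therapy". No repeat session is described.
- Table 1 lists general first aid as the intervention for controls, and "General first aid treatment + THJP" for the bloodletting arm.

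On blinding, the Discussion says that "it is impossible to blind the patients and acupuncturists". Section 2.1 has the acupuncturist learn the allocation just before treatment. Section 2.5 says that the statistics department is blinded.

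**The concern.** ITT keeps every randomised patient in the allocated group, because only randomisation makes the groups comparable. A set that also requires receipt of treatment is a treated-only, or modified, set. Giving it the ITT name tells readers they have a protection that the definition does not provide.

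Two features of this design make the wording matter. THJP is given once, so a requirement of at least one session reduces to whether it was received. The procedure also exists in one arm only and is given or omitted with the allocation known. A treated-only set is easiest to defend when blinding keeps non-receipt independent of allocation, and that protection is absent here.

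At stake are both primary outcomes, the Glasgow Coma Scale score (GCS) and COHb, since the definition governs every analysis. So is the value of the planned consistency check.

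**Working it through.** **Step 1. What the condition does under each meaning of a treatment session.**

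| Meaning | Controls | Bloodletting patient who misses THJP but gets first aid | Consequence |
|---|---|---|---|
| THJP only | None qualifies | Excluded | No control arm left, so hardly the intended meaning |
| The allocated treatment | Qualify through first aid | Can be excluded | Exclusion for missing THJP falls on one arm |
| Any treatment, shared first aid included | Qualify | Stays in | Nearly everyone qualifies and the condition is redundant |

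The text does not choose between the second and third rows.

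**Step 2. The consistency check.** The per-protocol set would presumably drop a patient who missed THJP, as a major violation. Under the second row the ITT set can drop the same patient. Both sets are then selected on treatment received, and agreement between them says nothing about the effect of that selection. Under the third row the ITT set is close to all randomised patients and the comparison is informative.

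**Step 3. Possible size under the second row.** The population definition carries no figure of its own. Inputs from section 2.5:

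- 31 patients per arm.
- COHb means 22.40 and 17.78, a planned difference of 22.40 − 17.78 = 4.62 points.
- SDs 3.65 and 5.68, pooled as √[(3.65² + 5.68²)/2] = 4.774.

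For reference, the stated 30 per group is roughly recovered with the larger SD, two-sided 5% and 90% power: 2 × (1.960 + 1.282)² × 5.68² / 4.62² ≈ 31.8, so 32. The pooled SD gives 23. Nothing below depends on this.

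Assumed, because the documents are silent: *k* bloodletting patients are excluded, they fare *g* SD worse than the rest of their arm, and there is no true effect.

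- Spurious shift in SD units: *s* = (*k*/31) × *g*. In COHb points: 4.774 × *s*.
- Standard error in SD units: √[1/31 + 1/(31 − *k*)].
- Two-sided type I error: 1 − Φ(1.96 − *s*/SE) + Φ(−1.96 − *s*/SE).

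| *k* (share of arm) | Shift, *g* = 0.5 | Error, *g* = 0.5 | Shift, *g* = 1.0 | Error, *g* = 1.0 |
|---|---|---|---|---|
| 1 (3.2%) | 0.08 | 0.051 | 0.15 | 0.052 |
| 2 (6.5%) | 0.15 | 0.052 | 0.31 | 0.057 |
| 3 (9.7%) | 0.23 | 0.054 | 0.46 | 0.066 |
| 5 (16.1%) | 0.39 | 0.061 | 0.77 | 0.093 |

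Worked case, *k* = 3 and *g* = 1.0: *s* = 3/31 = 0.097; shift = 4.774 × 0.097 = 0.46 points; SE = √(1/31 + 1/28) = 0.261; *s*/SE = 0.371; error = 0.066.

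Relative to the planned 4.62 points, the shifts run from 0.08/4.62 = 2% to 0.77/4.62 = 17%. With *g* = 0 the shift is zero and the error stays at 5%. With *g* negative the shift goes against THJP.

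**The case against.** The strongest defence is that shared first aid counts as treatment. The criterion is worded for patients in general, section 2.3.2 gives the bloodletting arm the same first aid as controls, and Table 1 lists first aid as intervention in both arms. On that basis nearly everyone qualifies and no bias follows. This stands as a possible meaning, so a reader who concludes that the condition fails however it is read goes too far. It does not rescue the sentence, which would then be redundant and would still leave the choice of meaning open until analysis.

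A reader might also infer that patients who miss THJP are the sicker ones, so that the bias favours THJP. No passage says so. Refusal, early waking or the lack of an acupuncturist could be unrelated to severity or could act the other way. Likewise, removing the two or three bloodletting patients with the very highest COHb gives simulated errors of 8.7% to 12.7% (assumed SD 5.0). That requires non-receipt to track COHb perfectly and is a worst case, not an expectation.

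Few patients may miss a brief procedure done on admission, so the numerical effect is probably small. Baseline GCS and COHb are recorded, and if the analysis used them they could absorb part of an imbalance. Both points are fair, but the article does not state the model.

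Blinding the statisticians does not answer the point, because non-receipt arises at the bedside before the data reach them.

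**Conclusion.** The label is wrong on the text as it stands: the set conditions on treatment received, its key term is undefined, and no all-randomised set is defined in its place. This is a rule the article states, not detail left to a fuller document.

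One-sided exclusion is a risk that the wording permits, not a certainty. It arises if a session means the allocated treatment and disappears if shared first aid counts. Where it arises, the ITT and per-protocol comparison cannot detect it.

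The direction and size of any bias cannot be established from the documents. The range of about 0.1 to 0.8 COHb points, with type I error of about 5% to 9%, rests entirely on the assumed numbers excluded and their assumed worse prognosis.

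**What to change.** Replace the definition in section 2.5 with:

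> The intention-to-treat population is all randomised patients, analysed in the group to which they were allocated, whether or not THJP or any other treatment was given.

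Use the outcomes already scheduled in both groups (sections 2.4.1 and 2.4.2, Table 1). None is made conditional on THJP, so no new measurement is needed. If a treated-only set is wanted, call it modified ITT, define a treatment session for each arm, and use the set only as a sensitivity analysis.

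The cost is a sentence or two, with no extra patients or procedures and the total unchanged at 62. The downside is some dilution from patients who miss THJP. If 1 to 5 of 31 miss it and gain nothing, the planned difference becomes 4.62 × 30/31 = 4.47 down to 4.62 × 26/31 = 3.87 points. The dilution is slight if few miss it, and it is the usual price of keeping the randomised comparison.
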